## Concomitant Therapy

For this protocol, participants engage in other treatments and there are no restrictions on medications. Psychotropic medication usage will be assessed at each assessment time point and documented in the relevant Medication Compliance Questionnaire, and any psychosocial interventions will be tracked using the Treatment History Interview.

### Rescue Therapy

In the event of significant concern of suicide risk, study clinicians or investigators may suggest to the parent of a study participant that they bring their child to be evaluated in the emergency department. A detailed safety protocol is attached as an appendix, and described in Section 8.2.

# STUDY INTERVENTION/EXPERIMENTAL MANIPULATION DISCONTINUATION AND PARTICIPANT DISCONTINUATION/WITHDRAWAL

## Discontinuation of Study Intervention/Experimental Manipulation

When a subject discontinues from the study intervention, whether voluntarily or involuntarily, but not from the study, remaining study procedures will be completed as indicated by the study protocol. If a clinically significant finding is identified (including, but not limited to changes from baseline) after enrollment, the investigator or qualified designee will determine if any change in participant management is needed. Any new clinically relevant finding will be reported as an adverse event (AE).

The data to be collected at the time of study intervention discontinuation will include the following:

- The reason(s) for discontinuing the participant from the intervention, and methods for determining the need to discontinue
- If the participant is due to complete assessments within 2 weeks of being discontinued from the study intervention, those assessments will be administered at the time of discontinuation; if the next scheduled assessments are more than 2 weeks from the discontinuation date, the discontinued participant will wait for the next scheduled assessment. Thereafter, the participant will be included in all future scheduled assessments, even though not participating in the intervention.

A participant may be involuntarily discontinued from the study intervention if the participant has an unexpected adverse reaction to intervention content, develops psychiatric symptoms that make continuation of the intervention impossible, or if clinical staff deem it is not clinically appropriate to continue the intervention during the psychiatric admission. The participant will also no longer receive the messages, if they are discontinued from the study.

## Participant Discontinuation/Withdrawal from the Study

Participants are free to withdraw from participation in the study at any time upon request.

An investigator may discontinue a participant from the study for the following reasons:

- Significant study intervention non-compliance, i.e. with respect to the individual sessions, unless varying compliance is an aspect of the study objectives
- Lost-to-follow up; unable to contact subject (see **Section 7.3, Lost to Follow-Up**)
- Any event or medical condition or situation occurs such that continued collection of follow-up study data would not be in the best interest of the participant or might require an additional treatment that would confound the interpretation of the study
- The participant meets an exclusion criterion (either newly developed or not previously recognized) that precludes further study participation

The reason for participant discontinuation or withdrawal from the study will be recorded on the Case Report Form (CRF). Subjects who sign the informed consent form and are randomized but do not receive the study intervention may be replaced. Subjects who sign the informed consent form, and are randomized and receive the study intervention, and subsequently withdraw, or are discontinued from the study, will not be replaced.

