**Skills to Enhance Positivity (STEP).** We developed the STEP intervention for adolescents admitted to an inpatient psychiatric unit due to suicide risk. STEP is a multi-modal, adjunctive intervention involving 4 individual sessions delivered on the inpatient unit, followed by text or email messaging post-discharge to assess mood and “push” positive affect strategies for up to three months. While STEP borrows heavily from preceding positive psychology interventions, such as Seligman’s positive psychotherapy (PPT) (32), importantly, it is also distinct. STEP does not address happiness, optimism, or meaning, which may feel unattainable or invalidating to patients in acute distress. Rather, it focuses on increasing attention and awareness to positive emotions and experiences that may be easily discounted by the cognitive constriction that often accompanies SI and SB. Consequently, specific exercises designed to increase attentional awareness (i.e., psychoeducation on functions of emotions, mindfulness, gratitude, and savoring) are practiced, and, in this sense, STEP more closely aligns with acceptance-based approaches to treating depression, which have become increasingly common (36).

MPIs [name] and [name] have conducted an open trial (N = 20) (37) and a pilot RCT (N = 52) (MH R34101272) (38) of STEP; both trials indicated excellent feasibility. The samples were characteristic of inpatient settings, i.e., high rates of comorbidity, especially mood disorders (92%), NSSI (96%), and past SA 52%). (See 43, 44 for details). We will recruit participants from the same site, thus anticipate the same clinical features in the proposed study. On average, 81% of in-person sessions were completed in the open trial, and 83% in the RCT. Participants responded to the text-messaging component of STEP on 74% of days in the open trial and 70% of days in the RCT. Based on feedback received from the open trial in which respondents requested text messaging be extended, we offered an optional 3-month extension of texts 3x/week to those randomized to STEP in the RCT; 52% opted for this extension without any financial incentives. Acceptability ratings for in-person sessions and text messaging, as well as the specific exercises introduced in STEP, were high for both adolescents and parents in both trials, with 95% in Open and 88% in RCT rating quality of services as either good or excellent.

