### Administration and/or Dosing

*In-person phase*. STEP consists of 4 individual, treatment sessions typically completed in days 4 – 7 on the unit. In the pilot trial, all participants were started on the inpatient unit and 65% completed all sessions on the unit with the remainder, typically session 4, scheduled after discharge. In the current study, we will add procedures to increase parent engagement with STEP via a handout which will be provided after consenting and randomization to the STEP condition at the time of discharge. This handout describes the study goals and outlines ways in which parents/guardians can support their children throughout the study. The content of the sessions is described in the table below. Participants will be pulled from other therapeutic activities on the unit for their STEP session so that STEP participants will not receive more therapeutic contacts while hospitalized than the ETAU participants. Sessions are designed to maximize flexibility such that if not all of the content is delivered in one session, it can be delivered in the following session. For participants who have a shorter length of stay or are discharged early, the individual STEP sessions might be compressed to be able to deliver the intervention in a timely manner prior to their discharge. Four videos with content derived from the treatment manual will be used to help supplement the skills covered in the STEP sessions.

| Table 2. STEP In-Person Sessions |  |
| --- | --- |

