handled with multiple imputations, with assumptions checked with sensitivity analyses (76), is pre-specified (as are all aspects of our analysis plan). We will adhere to intent-to-treat principles, and all aspects of data analysis will be pre-specified as reflected in this proposal, and with modification following proposal review and discussions with program and our Data Safety and Monitoring Board. Preliminary analyses will include descriptive statistics to examine the distributional and psychometric properties of the variables (e.g., normality, internal consistency). Variables will be transformed to better approximate normality if this is necessary given the observed distribution and the assumptions of the analysis model. We will also examine post-inclusion attrition by comparing study completers to dropouts on sociodemographic, baseline data, and psychotropic medication usage to determine if they differ systematically. We will examine the success of the stratified randomization by examining between-group differences at baseline. Preliminary analyses may also include analyses of adverse events, the progress of recruitment and retention, and data processing and quality markers as the study progresses. Daily mood monitoring data is not included in outcome analyses because it is conceptualized as part of this adjunctive intervention and only collected in one condition.

Missing data. To accommodate attrition and other sources of missingness, we will utilize the method of multiple imputation by chained equations. At least 50 replicates of each missing value will be generated for inclusion in analyses. This method can accommodate clustering of repeated measures at the level of the. We have previously used these methods in successful analyses of trials of exercise interventions.

Statistical computing. Modeling will be performed using Stata (Stata Corp, College Station, TX, version 16.2 or higher) and R software (R Foundation for Statistical Computing, Vienna, Austria, version 4.0 or higher) and Mplus (version 8.4 or higher, Muthen & Muthen, Los Angeles, CA). Analyses and reporting will be executed and archived to ensure full replicability and reproducibility by analysts at Brown University, under the direction of the project methodologist, [name].

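### Section 7.2 lets an investigator end study participation for missed individual sessions, which only STEP has, and nothing says how this fits with the rule in Section 7.1 that keeps such participants in follow-up

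*Protocol*

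**What the plan says.** Section 7.2 (Participant Discontinuation/Withdrawal from the Study) opens its list with "An investigator may discontinue a participant from the study for the following reasons". The first reason is "Significant study intervention non-compliance, i.e. with respect to the individual sessions, unless varying compliance is an aspect of the study objectives". The section does not define what makes non-compliance significant.

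Section 7.1 (Discontinuation of Study Intervention/Experimental Manipulation) covers a neighbouring case: "When a subject discontinues from the study intervention, whether voluntarily or involuntarily, but not from the study, remaining study procedures will be completed as indicated". It adds that "the participant will be included in all future scheduled assessments, even though not participating in the intervention".

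Section 9 says "We will adhere to intent-to-treat principles" and handles missing values by multiple imputation with chained equations, with sensitivity analyses of the assumptions.

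The sessions belong to STEP. Under Administration and/or Dosing, "STEP consists of 4 individual, treatment sessions typically completed in days" 4 to 7 on the unit. The comparison condition is the unit's usual treatment plus safety-plan and healthy-habit messages, with no individual sessions delivered by the study.

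**The concern.** In an intent-to-treat comparison, outcomes should be sought from everyone randomized, whatever treatment they took up. A rule that ends follow-up because of attendance makes the availability of outcomes depend on behaviour after randomization. Here the behaviour can occur in one arm only, and anyone applying the rule necessarily knows that the participant is in STEP. If those removed differ in prognosis from those who stay, the two arms as observed are no longer the two arms as randomized.

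The outcomes at stake are the primary ones: suicidal events, active suicidal ideation and depression at 6 months, and suicidal events at 12 months. Imputation repairs such a loss only to the extent that observed data explain it. Otherwise the missing STEP values are filled largely from STEP participants who attended.

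**Working it through.** The protocol states no figure on this point, so there is none to reproduce. The check is mainly a comparison of passages.

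**1. Does the ground end outcome collection?** Section 7.1 is about stopping the intervention and Section 7.2 about leaving the study. Another reason in the 7.2 list refers to further collection of follow-up data not being in the participant's interest. That supports reading discontinuation under 7.2 as the end of assessments.

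**2. Can it reach both arms?** Only STEP has individual study sessions. ETAU patients attend therapy on the unit, but as usual care and not as study intervention. The ground therefore reaches STEP only.

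**3. Do 7.1 and 7.2 contradict each other?** Not literally. Section 7.1 is limited to someone who stops the intervention without leaving the study. A STEP participant who misses sessions could be retained under 7.1 or removed under 7.2, and nothing decides which. This is an overlap with no stated boundary.

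**4. Does the exception clause settle it?** The ground lapses if varying compliance is part of the study objectives. Section 3 lists no compliance objective. The Significance paragraph of the Background, however, names the number of sessions received as a potential moderator to explore. The protocol does not say whether that triggers the exception, so sites could read it either way.

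**5. Hypothetical size.** Let p be the true event rate in the whole STEP arm, f the fraction of STEP removed, and k the ratio of the removed participants' rate to p. Since p = f·k·p + (1 − f)·p_kept, the rate in those kept is

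p_kept = p(1 − f·k)/(1 − f).

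Inputs: p = 0.38, the ETAU rate in Aim 1D of Section 9, used for both arms so that there is no true effect. The values f = 0.10 to 0.17 and k = 0.75 to 1.5 are assumptions; the protocol gives neither.

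| f | k | Calculation | Observed STEP rate | Shift from 38% |
|---|---|---|---|---|
| 0.10 | 1.25 | 0.38 × 0.875/0.90 | 36.9% | 1.1 points in favour of STEP |
| 0.17 | 1.50 | 0.38 × 0.745/0.83 | 34.1% | 3.9 points in favour of STEP |
| 0.10 or 0.17 | 1.00 | 0.38 × 0.90/0.90 or 0.38 × 0.83/0.83 | 38.0% | none |
| 0.10 | 0.75 | 0.38 × 0.925/0.90 | 39.1% | 1.1 points against STEP |
| 0.17 | 0.75 | 0.38 × 0.8725/0.83 | 39.9% | 1.9 points against STEP |

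These are complete-case figures. They do not model the planned imputation, its sensitivity analyses or events found in the health record.

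**6. Power.** This is a side issue. With 81 per group (the 162 of Section 9), 38% against 17%, and an assumed two-sided 5% level, the uncorrected two-proportion normal approximation gives 85.6%; with a continuity correction it is 81.1%, close to the stated 80%. Removing a further 10% or 17% from STEP alone lowers the uncorrected value to 83.5% or 81.7%. The cost in power is minor; any harm would come through bias.

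**The case against.** The strongest reply is that the rule is permissive and may seldom be used. Justification for Intervention sets minimum acceptable participation at one in-person session plus any engagement with the messages. All pilot participants began on the unit, and sessions may now be compressed for short stays. If that minimum marks compliance, few would qualify for removal. This stands as a limit on likely size, but Section 7.2 does not refer to the minimum.

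A reader might infer from the pilot that 17% or 35% of STEP would be removed. The document does not support that. The protocol reports "On average, 81% of in-person sessions were completed in the open trial, and 83% in the RCT"; the complement of 83% is a share of sessions, not of participants. The 35% is the complement of the 65% who finished all sessions on the unit, and the rest, typically lacking session 4, had it scheduled after discharge. Neither figure measures non-compliance.

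A reader might also infer that the rule must favour STEP, on the view that those who miss sessions fare worse. No passage shows this. The obstacle to completing sessions that the protocol discusses is a short stay or early discharge, which need not mean a worse prognosis.

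Finally, Section 9 expects suicidal events to be obtainable from the electronic record as well, and plans sensitivity analyses. Both help. Record data may recover some suicidal events, but not BDI-II scores or interview-rated active ideation.

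**Conclusion.** The point holds as a flaw in the rule, not as a demonstrated bias. The protocol authorizes an undefined, discretionary, STEP-only ground for ending outcome collection. It leaves the boundary with Section 7.1 and the exception clause unresolved, and the ground sits badly with intent-to-treat. It would go too far to say that 7.1 states the opposite of 7.2, that outcome data will be lost, or that a false win for STEP becomes more likely by a known amount.

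On the assumed inputs the shift runs from 3.9 points in favour of STEP to 1.9 points against, with none if those removed have average risk. The number removed and their prognosis are not in the document, so this range illustrates sensitivity and does not estimate bias. It should be fixed, because the repair is small and lost outcomes cannot be recovered by a later analysis plan. The documents do not support a more serious rating.

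**What to change.** Delete the non-compliance bullet from Section 7.2. State there that non-compliance with sessions or messages is recorded in the REDCap clinician dashboard already described under Section 6.4 (adherence), that it does not end study follow-up, and that Section 7.1 governs outcome assessments for anyone who stops or misses the intervention. The change concerns outcome collection only and leaves decisions about continuing the intervention as they are.

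If the effect of actually receiving STEP is of interest, a complier average causal effect with randomization as the instrument could be added as an optional secondary analysis.

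The cost is one deleted bullet and a sentence or two by amendment. No new procedure is needed, since Section 7.1 already schedules these assessments and attendance is already tracked.

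### Section 7.2 lets randomized non-starters be replaced and session non-compliers be withdrawn, in practice only in STEP, without saying that they stay in follow-up and in the intent-to-treat analysis

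*Protocol*

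**What the plan says.** Section 7.2 (Participant Discontinuation/Withdrawal from the Study) contains three relevant rules.

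- **Replacement.** "Subjects who sign the informed consent form and are randomized but do not receive the study intervention may be replaced". By contrast, those who sign consent "and are randomized and receive the study intervention, and subsequently withdraw, or are discontinued from the study, will not be replaced". Replacement therefore turns on receipt, which is known only after randomization.
- **Session non-compliance.** Under the lead-in "An investigator may discontinue a participant from the study for the following reasons", the first ground is "Significant study intervention non-compliance, i.e. with respect to the individual sessions, unless varying compliance is an aspect of the study objectives".
- **Confounding treatment.** Another ground covers an event, condition or situation that "might require an additional treatment that would confound the interpretation of the study".

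Section 7.1 covers participants who stop the intervention but not the study. They complete the remaining procedures: "Thereafter, the participant will be included in all future scheduled assessments, even though not participating in the intervention". Section 9 states: "We will adhere to intent-to-treat principles".

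**The concern.** Intent-to-treat needs everyone randomized to be followed as far as possible and analysed in the assigned arm. A rule that swaps out or withdraws people according to what they did after randomization selects the sample. If it operates in one arm only, the groups compared are no longer those that randomization formed.

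The confounding-treatment ground raises a related problem. In this population, additional treatment is often the response to deterioration, and emergency evaluation and psychiatric hospitalization belong to the suicidal-event outcome. A participant could be withdrawn because of care that accompanies an endpoint.

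These are rules of trial conduct. A statistical analysis plan can define the analysis set, but it cannot bring back interviews and questionnaires that were never done.

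**Working it through.** **Which arm do the rules reach?** Section 7.2 names no arm, so this is an inference from usage.

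- Overall Design defines the study intervention as STEP.
- Administration and/or Dosing says that the comparison arm does not get mood monitoring or positive affect skills, because these belong to the study intervention.
- Scientific Rationale for Study Design gives the four study sessions to STEP, while ETAU participants attend usual therapy.

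Read literally, the replacement sentence would make every ETAU participant replaceable, which cannot be meant. An ETAU participant also has no study sessions to miss. Both rules therefore work in STEP only.

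**Does the qualifier switch off the non-compliance ground?** The rule lapses if varying compliance is an aspect of the study objectives. The Significance text in Background plans to explore the number of sessions received and engagement as potential moderators. The Objectives and Endpoints table does not list compliance. The protocol leaves the matter open.

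**How is a session non-complier handled?** If classed as stopping the intervention, the participant stays in all assessments (Section 7.1). If classed as non-compliant, the participant may be withdrawn from the study (Section 7.2). No criterion says which applies.

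**Is the confounding-treatment ground consistent with the rest?** Known Potential Risks allows or encourages any clinically indicated treatment. Concomitant Therapy places no restriction on medication and expects other treatments. Exclusion Criteria keeps those admitted to residential care after enrolment. The ground conflicts with all three, in either arm.

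**Size.** The plan gives no figure to reproduce. The following is an illustration under no true effect.

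Inputs: an event rate of 38% in both arms (the ETAU rate in Aim 1D; the pilot had 10/26 = 38%); n per arm of 81 (half of the 162 used for power) or 108 (half of 216); two-sided 5% level (assumed, since the protocol states no value). The share f of STEP replaced or withdrawn, and their event rate q, are assumptions. The calculation treats those affected as lost to the analysis and the arm as refilled to n.

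- Retained STEP rate: p_S = (0.38 − f·q)/(1 − f), and d = 0.38 − p_S.
- Rejection rate: Φ((d − 1.96·SE0)/SE1) + Φ((−d − 1.96·SE0)/SE1), where SE0 = √(2·p̄(1 − p̄)/n), SE1 = √((0.38·0.62 + p_S(1 − p_S))/n), and p̄ is the mean of the two rates.

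Example with f = 15%, q = 65%, n = 108: p_S = (0.38 − 0.0975)/0.85 = 0.332; d = 0.048; SE0 and SE1 are both about 0.065; the two tails sum to 11.3%.

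| f | q | Retained STEP rate | Difference (points) | Rejection, n = 81 | Rejection, n = 108 |
|---|---|---|---|---|---|
| 5% | 45% | 37.6% | 0.4 | 5.0% | 5.0% |
| 10% | 55% | 36.1% | 1.9 | 5.7% | 5.9% |
| 15% | 55% | 35.0% | 3.0 | 6.8% | 7.4% |
| 15% | 65% | 33.2% | 4.8 | 9.7% | 11.3% |

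The sign depends on q. If those affected were at lower risk, say f = 10% and q = 25%, then p_S = (0.38 − 0.025)/0.90 = 39.4%, a shift of 1.4 points against STEP.

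**The case against.** The case on the other side has real weight.

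- **Replacement is not removal.** A reader might infer that replaced participants are deleted and that Section 7.2 flatly contradicts intent-to-treat. The text does not say so. An extra participant could be enrolled while the replaced one is followed and analysed as randomized, which would be compatible with Section 9. What stands is that the protocol is silent where it needs to be explicit, and that the rule is discretionary with no criterion.
- **Sections 7.1 and 7.2 address different levels.** It is tempting to read Section 7.1 as the direct opposite, but it is limited to people who stop the intervention and not the study. Only the narrower overlap stands: a session non-complier can be routed either way.
- **The pilot does not show many would be affected.** Pilot participants completed 83% of sessions, and 65% finished all sessions on the unit. But all pilot participants started on the unit, and the outstanding sessions, typically the fourth, were scheduled after discharge. These figures support no particular share removed.
- **Direction.** A reader might infer that poorly engaged youth are at higher risk, so that bias favours STEP. The reason the protocol gives for compressed sessions is a short stay or early discharge, and it does not say whether such youth are at higher or lower risk.
- **Mitigation.** Consent covers auditing of hospital records for emergency and inpatient admissions, and Section 9 expects event data from the health record. It also plans multiple imputation with sensitivity analyses. Records would recover some suicidal events. They do not supply interview-rated active ideation or BDI-II scores, and imputation need not correct withdrawal tied to unmeasured prognosis.

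**Conclusion.** The point holds as a gap and an internal inconsistency in the conduct rules. Section 7.2 permits replacement and study-level withdrawal on post-randomization grounds, two of which can in practice arise only in STEP. It does not say that those affected stay in follow-up and analysis. Used as written, the rules could undermine the comparison that Section 9 promises.

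The documents do not establish that bias will occur, which way it would run or how large it would be. The illustrations go from no visible effect (5.0% rejection with 5% affected at 45% risk) to about 11% (15% affected at 65% risk). They rest on assumed shares and risks, and on those affected being lost to analysis. The one-arm reading rests on how the protocol uses its terms, and the non-compliance ground may be inactive if its qualifier applies.

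**What to change.** Amend Section 7.2 and align it with Sections 7.1 and 9:

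1. Delete the replacement sentence, or add that any replaced participant is still followed and analysed as randomized.
2. Remove session non-compliance and confounding additional treatment as reasons for withdrawal from the study, so that these participants follow the Section 7.1 retention rule.
3. State in Section 9 that all randomized participants are analysed in their assigned arm, whether or not they received any sessions.

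Keep withdrawal on request, the best-interest ground and the other existing grounds. Limiting withdrawal to request or inability to assess would strip out a protection for suicidal minors and is not needed here. The change concerns data collection and analysis only and implies nothing about clinical care.

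The cost is a short amendment, with a few non-starters counting toward the 216. The power plan already works with 162 of 216 (75%).
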